### Outcome measures

#### Primary outcome

Our assessment of self-harm will consist of three parts: (A) a brief interview, (B) completion of the Risk Taking and Self-Harm Inventory for Adolescents (RTSHIA)^35^ and (C) the provision of support and advice.

#### Part A: interview

Young people will be asked ‘have you ever hurt yourself on purpose in any way (eg, by taking an overdose of pills or by cutting yourself) over the past 3 months?’ which was taken from the Avon Longitudinal Study of Parents and Children (http://www.alspac.bris.ac.uk).^36^ Young people are asked to consider the last 6 months at baseline and the last 3 months at follow-ups. Those who answer yes will be asked further questions about frequency, method, reason for self-harming, whether they sought medical help and suicidal intent.

#### Part B: RTSHIA

Our primary outcome is self-reported self-harm assessed by the self-harm inventory of the RTSHIA. The RTSHIA was developed in the UK for use with adolescents (aged 11–19 years).^35^ The self-harm inventory consists of 18 items and assesses the presence and frequency of a range of intentional self-injuries (eg, cutting, burning, self-hitting, self-poisoning). The frequency of each item is rated on a 4-point scale (never, once, more than once and many times) over a defined period. At baseline, the young person is asked to consider the 6 months before their initial assessment. For the 12-week and 6-month assessment, the young person considers the 3-month period since their last assessment. Each item is then scored (0, 1, 2, 3) and totalled to provide a current self-harm score. The RTSHIA has good reliability and validity.^22 35^ We will analyse total scores and use this information to categorise changes in self-harm from baseline to 12 weeks and 6 months as reduced/stopped versus same/increased.

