### Setting and participants

Participants will be recruited through CAMHS provided by Oxford Health NHS Foundation Trust, covering Bath and North-East Somerset, Swindon, Wiltshire, Buckinghamshire and Oxfordshire.

Young people will be eligible if they: (1) are receiving treatment from CAMHS at the time of referral, (2) have self-harmed at least two times in the last 12 months and (3) are aged between 12 and 17 years.

Exclusion criteria are: (1) a diagnosis of psychosis, (2) a significant learning disability which would interfere with the young person’s ability to use the app, (3) young people with active suicidal plans or (4) safeguarding concerns where the young person has suffered abuse within the last 6 months or is the subject of a safeguarding investigation.

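### Self-harm is recalled over 6 months at baseline but 3 months at follow-up, so the planned reduced/stopped category drifts towards improvement in both arms without any true change; the primary comparison is unaffected

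*Protocol article*

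**What the plan says.** All references are to the protocol article.

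- **Part B: RTSHIA, baseline window.** "At baseline, the young person is asked to consider the 6 months before their initial assessment".
- **Part B: RTSHIA, follow-up window.** "For the 12-week and 6-month assessment, the young person considers the 3-month period since their last assessment".
- **Part B: RTSHIA, scale.** "The self-harm inventory consists of 18 items". "The frequency of each item is rated on a 4-point scale (never, once, more than once and many times) over a defined period". "Each item is then scored (0, 1, 2, 3) and totalled to provide a current self-harm score".
- **Part B: RTSHIA, derived outcome.** The totals will be used to "categorise changes in self-harm from baseline to 12 weeks and 6 months as reduced/stopped versus same/increased".
- **Part A: interview.** The same mismatch: "Young people are asked to consider the last 6 months at baseline and the last 3 months at follow-ups".
- **Setting and participants.** To be eligible, young people must "have self-harmed at least two times in the last 12 months".

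No section rescales the score for window length, collects a 3-month baseline, or defines an unchanged score in a way that allows for the window. The Statistical analysis section names the total RTSHIA score as the primary outcome and assigns logistic regression to binary secondary outcomes.

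**The concern.** The RTSHIA total is built from frequencies over a stated period. Halving the period lowers the expected score at an unchanged rate of self-harm. A category defined by the sign of follow-up minus baseline takes on that fall and reports it as benefit.

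Two uses of the category are at stake:

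1. The percentage reduced/stopped in each arm, read as a description of how participants fared.
2. The between-arm comparison of that percentage. If usual care is already high through the window alone, little room is left for the app to do better.

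There is also a small problem at the floor. Eligibility looks back 12 months and baseline only 6, so a participant can enter with a score of 0, remain at 0, and be counted with same/increased.

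**Working it through.** **1. The plan's own figure.** Inputs from Sample size: difference 2, SD 3.6, power 90%, alpha 0.05 (taken as two-sided). n per group = 2 × (1.960 + 1.282)² × 3.6² / 2² = 68.1, rounded up to 69. The stated 69 reproduces. It rests on the total score compared between arms, not on the category.

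**2. One item at a constant rate.** Score 0 for none, 1 for one, 2 for two or more, 3 from a count k upwards. The documents give no k, so 4, 6 and 10 were tried. Entries are baseline score (6 months) → follow-up score (3 months).

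| Episodes per 3 months | k = 4 | k = 6 | k = 10 |
|---|---|---|---|
| 1 | 2 → 1 | 2 → 1 | 2 → 1 |
| 2 | 3 → 2 | 2 → 2 | 2 → 2 |
| 3 | 3 → 2 | 3 → 2 | 2 → 2 |
| 5 | 3 → 3 | 3 → 2 | 3 → 2 |
| 10 | 3 → 3 | 3 → 3 | 3 → 3 |

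The score falls or stays level and never rises. It stays level when both counts fall in the same response band, including when both sit at the cap.

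**3. Whole score, no true change (simulation).** All rate inputs are assumptions:

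- mean number of methods in use: 1, 2, 4 or 7 of the 18 items;
- mean episodes per method per 3 months: 0.5, 1, 3 or 8, varying by a gamma distribution with shape 0.5 or 2;
- Poisson counts; k = 4, 6 or 10.

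That gives 4 × 4 × 2 × 3 = 96 scenarios.

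| Unchanged participants labelled reduced | 6 v 3 months | 3 v 3 months |
|---|---|---|
| All simulated participants | 27% to 92% | 18% to 43% |
| At least 2 episodes in the baseline window | 27% to 93%, median 74% | 18% to 74%, median 42% |

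One example: 4 methods, 1 episode each per 3 months, shape 0.5, k = 6. Unequal windows give 67% reduced, 22% same and 11% increased. Matched windows give 34%, 31% and 34%.

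In the restricted row the share labelled reduced passes 50% in 92% of scenarios. It does so in 13 of the 14 whose follow-up SD is near the plan's 3.6 (3.0 to 4.2). The restriction is stricter than the eligibility rule and adds regression to the mean, so these are upper-side readings.

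**4. Between-arm comparison of the category, 69 per arm.** Assumed: usual care unchanged, app halves the rate; shape 0.5, k = 6, same restriction. Power = Φ(|p₁ − p₂| / √[(p₁(1 − p₁) + p₂(1 − p₂)) / 69] − 1.96).

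| Methods, rate | 6 v 3: usual care / app | Power | 3 v 3: usual care / app | Power |
|---|---|---|---|---|
| 2, 1 | 0.72 / 0.90 | 0.78 | 0.46 / 0.75 | 0.95 |
| 4, 1 | 0.76 / 0.92 | 0.75 | 0.44 / 0.77 | 0.98 |
| 4, 3 | 0.74 / 0.93 | 0.86 | 0.38 / 0.76 | >0.99 |
| 7, 3 | 0.84 / 0.97 | 0.79 | 0.40 / 0.83 | >0.99 |

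Second row, unequal windows: 0.16 / √[(0.1824 + 0.0736) / 69] = 0.16 / 0.0609 = 2.63; 2.63 − 1.96 = 0.67; Φ(0.67) = 0.75.

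**5. Would a binary outcome without a baseline do better?** Any self-harm in the past 3 months was tried under a second assumed model: mean 3 to 25 acts per 3 months, gamma shape 0.7 to 2, at least 2 acts in 12 months, app halves the rate, 69 per arm. From 82% to nearly 100% of usual care score positive. Power is about 0.51 to 0.66 at 3 acts and 0.10 to 0.28 at 12 to 25 acts. In the same model the planned category has 0.46 to 0.65, and a category on matched 3-month windows has 0.81 to over 0.99.

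**The case against.** The strongest reply is that nothing essential to the trial depends on this category. That is largely right.

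- **Primary result.** It compares 12-week totals between randomised arms, both recalled over 3 months. The self-harm adjuster is the minimisation variable, which covers the last 4 weeks (Randomisation). The 6-month model uses the two follow-up scores adjusted for baseline, and a covariate need not share the outcome's window. A reader might infer that the primary analysis is biased or the sample size wrong; neither follows.
- **The 2-point target.** A reader might set the artificial within-arm fall against it. The target is a difference between groups, and the window effect is common to both, so the two are not comparable.
- **Most unchanged participants.** A reader might infer that the rule labels most of them improved. That depends on rates and a top-response count that the documents do not give. It fails for few methods at low rates, and for few methods used so often that items stay at the cap. Matched windows also label some unchanged participants reduced, so only the excess is due to the window.
- **The open study's 73%** (Background). Its recall windows are not given, so how the two percentages would compare is unknown.
- **Harm.** Increases in self-harm are also collected as adverse events, so their detection does not rest on this category.
- **The floor.** In a rerun with 3 to 25 acts per 3 months, only 0.1% to 4% had a baseline score of 0. An analysis plan could settle their handling.

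What the reply does not remove is the rule itself. The windows and the category are both stated, and an analysis plan cannot recover a 3-month baseline that was never asked for.

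**Conclusion.** The category is wrong as written. Its direction follows from the text alone: with no true change, unequal windows push participants in both arms towards reduced. The size is uncertain, possibly a majority: 27% to 92% against 18% to 43% with matched windows, under the assumed rates and thresholds in the working.

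Two consequences follow. The within-arm percentages cannot be read as improvement. The between-arm comparison of the category is weaker than it need be: in the four illustrative scenarios with the rate halved, power is 0.75 to 0.86 instead of 0.95 to over 0.99. The finding is confined to the change category and to any within-arm change from the 6-month baseline score.

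**What to change.** 1. For participants still to be recruited, also ask baseline RTSHIA and Part A for the last 3 months, and derive the change category only from matched 3-month windows.
2. For participants with only a 6-month baseline, drop the category. Use the baseline score solely as a covariate when comparing follow-up totals between arms, and report no within-arm change from it.
3. Do not substitute any self-harm in the past 3 months as the main binary outcome, since nearly all repeat self-harmers may score positive. At most, report it descriptively.

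The cost is one extra recall prompt at baseline and a wording change, to be settled before database lock. The category would exist only for later recruits: Trial status puts the start of recruitment at January 2020 and its end around June 2022. The number available, and so the precision of that comparison, depends on when the prompt is added.

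### The 'reduced/stopped' versus 'same/increased' category compares a 6-month baseline RTSHIA total with a 3-month follow-up total, so an unchanged rate of self-harm tends to be classed as 'reduced' in both arms

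*Protocol article*

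**What the plan says.** All of this is in the Protocol article.

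- **Measure** ('Part B: RTSHIA'): "The self-harm inventory consists of 18 items". Each item has four ordered frequency answers, from never to 'many times'. "Each item is then scored (0, 1, 2, 3) and totalled to provide a current self-harm score".
- **Baseline window** (same section): "At baseline, the young person is asked to consider the 6 months before their initial assessment".
- **Follow-up windows** (same section): "For the 12-week and 6-month assessment, the young person considers the 3-month period since their last assessment".
- **Use**: besides analysing totals, the plan will "categorise changes in self-harm from baseline to 12 weeks and 6 months as reduced/stopped versus same/increased". It states no rescaling for window length, no common window and no margin for 'reduced'.
- **Interview** ('Part A: interview'): the same windows, "Young people are asked to consider the last 6 months at baseline and the last 3 months at follow-ups". The article plans no change score from the interview.
- **Analysis** ('Statistical analysis'): the primary outcome is the RTSHIA total, compared between arms at 12 weeks. Binary outcomes go to logistic regression.

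**The concern.** The item answers are counts in coarse form, and the baseline window is twice as long as either follow-up window. The baseline total can therefore exceed the follow-up total without any change in behaviour, and the rule would record that as improvement. Summed ordinal scores cannot be halved to put the two on one footing.

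Three things are at stake:

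- any published percentage 'reduced or stopped' within an arm;
- the ability of the category to show worsening, which matters in a self-harm trial;
- the sensitivity of the logistic comparison between arms, if most of both arms fall into the favourable class.

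The analysis plan is still to be agreed before database lock. It can change the rule, but it cannot recover a 3-month baseline from a 6-month answer.

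**Working it through.** **1. The plan's own figure.** Inputs from 'Sample size': difference 2, SD 3.6, power 90%, alpha 0.05 (taken as two-sided). n = 2 × (1.960 + 1.282)² × 3.6² / 2² = 2 × 10.51 × 12.96 / 4 = 68.1, rounded up to 69 per group. This reproduces the plan. It rests on a between-arm difference in points, so the change category does not enter it.

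**2. Direction.** Let an act occur at a constant monthly rate r. The expected count is 6r at baseline and 3r at follow-up. The item score never falls as the count rises, so with one reading of 'many times' the expected follow-up score is lower or equal.

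- Example: two evenly spaced acts in 6 months score 2 at baseline. One act in 3 months scores 1. Four such items give 4 × 2 = 8, then 4 × 1 = 4: 'reduced', with nothing changed.
- Counter-example: 30 acts in 6 months is 15 in 3 months. If 'many times' starts at 10, both score 3 and there is no artefact.

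The direction is clear, but the size depends on frequencies that the documents do not give.

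**3. Worsening.** If the rate doubles, the follow-up count has expectation 2r × 3 = 6r, the same as at baseline. With Poisson counts and one reading of 'many times', the two totals then have the same distribution. 'Increased' is no likelier than 'reduced', so its chance is at most one half. Simulation of a doubled rate gave 35-41% classed 'increased', against 59-76% with matched 3-month windows.

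**4. Size with no true change.** Simulated inputs: 18 items, Poisson counts, scores 0-3 summed, and any fall in the total counted as 'reduced'. Assumed, because the documents do not state them: a mean of 1-6 methods used, a mean of 1-30 episodes per method in 6 months, and 'many times' starting at 4, 6 or 10 episodes. That threshold was either fixed or roughly halved for the shorter window. Participants had at least two episodes in the baseline window. There were 720 scenarios; equal windows here means 6 months both times.

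| Setting | Classed 'reduced', mean | Range |
|---|---|---|
| Equal windows | about 33% | 7-52% |
| 6 v 3 months, fixed threshold | about 66% | 20-85% |
| 6 v 3 months, scaled threshold | about 55% | 14-80% |

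The 6 v 3 share exceeded the equal-window share in all 720 scenarios, and exceeded 50% in about 75% of them. Among scenarios with a baseline SD of 3.1-4.1, the range was 31-83% and about 83% exceeded 50%. A separate, narrower set of settings with SDs near 3.6 gave 68-79%, against 40-51% with matched windows.

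**5. Between-arm contrast, 69 per arm.**

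- Rate cut by 30% in one arm, in one setting of the grid: 79% v 90% 'reduced' (difference 11 points, power 0.42) with 6 v 3 months, against 41% v 63% (22 points, power 0.72) with equal windows. Across three settings, power was 0.42-0.62 against 0.72-0.82.
- Rate halved, in the narrower settings: power 56-74% for the planned category and 76-96% with matched windows. A binary of any self-harm versus none in the last 3 months had 27-57%.

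**The case against.** The strongest reply is that nothing decisive rests on this category. The powered outcome is the RTSHIA total at 12 weeks, both arms are then rated over the same 3 months, and randomisation makes the mismatch identical in the two arms. That stands, and it limits the point to a secondary category.

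A second reply is that the article gives no margin for 'reduced' and leaves detail to the analysis plan. That is true, and the simulations assume that any one-point fall counts. A margin would change the percentages, but the totals would still cover unlike periods, and the windows are fixed when the data are collected.

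Stronger readings are tempting, and the documents do not support them:

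- *Most unchanged participants will be classed as 'reduced'.* This is likely under many assumptions but not established. It fails where a few methods are used very often, because items stay at 'many times' in both windows.
- *The percentage 'reduced' would be mainly a recall artefact.* Chance fluctuation alone gives about 33% with equal windows. On the grid averages, the mismatch adds 66 − 33 = 33 points or 55 − 33 = 22 points, which is half of the total or less.
- *The mismatch favours BlueIce or undermines the primary result.* It does neither.
- *The 73% reduction or cessation in the earlier open study ('Background') shows the same artefact.* That study's windows are not stated, so no comparison can be drawn.

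**Conclusion.** The point holds in a limited form and should be fixed. As written, the category mixes window length with behaviour and leans towards 'reduced' in both arms. An unchanged rate may be classed 'reduced' in a majority of cases: about 14-85% across assumed frequencies and roughly 70-80% in the narrower settings with SDs near 3.6, against about 40-50% there with matched windows. An SD near 3.6 does not settle the figure, since the wider grid still ran from 31% to 83% at that spread.

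The direction rests on the stated windows and scoring. The size rests on assumed frequencies, on how respondents read 'many times', and on counting any fall as 'reduced'. The consequences are within-arm percentages that cannot be read as change, hidden worsening and a compressed between-arm contrast. The 12-week comparison of totals and the 69 per group are untouched.

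**What to change.** 1. Do not report 'reduced/stopped' versus 'same/increased' from the 6-month baseline total as a change in self-harm.
2. If the category is wanted, add a 'last 3 months' RTSHIA rating at baseline for participants still to be recruited ('Trial status' expects recruitment to run to around June 2022), and derive the category only from matched 3-month windows. Cost: one extra recall column, and no change category for those already enrolled.
3. For all participants, rely on the between-arm comparison of 3-month totals at 12 weeks and 6 months. This uses data already planned.
4. As a supplementary binary, use any self-harm item above 0 in the last 3 months, analysed with the planned logistic regression. It removes the window artefact and costs only wording in the analysis plan. It answers a narrower question (cessation only) and does not recover power: in the halved-rate settings it had less than the category it would stand beside. The plan should say so.

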#### Part C: support and advice

At the end of the assessment, young people will be given a list of contacts they can call if they are feeling worried about themselves. These include NHS 111, Childline and the Samaritans.

#### Secondary outcomes

The MFQ^37^ is a self-report questionnaire for depression recommended by National Institute for Health and Care Excellence (NICE) consisting of 33 items rated as either ‘true’ (scores 2), ‘sometimes true’ (scores 1) or not true (scores 0). The MFQ has high criterion validity and correlates well with other measures of depression.^37^ A total score of 27 and above is associated with major depression, 20 with mild depression and 16 with no mood disorder. The Hopelessness Scale for children, adapted from Beck’s Hopelessness Scale,^38 39^ consists of 17 true–false items measuring hopelessness and negative expectations for the future. Items endorsed as ‘true’ are summed, with higher scores indicating greater hopelessness. The Hopelessness Scale for children has been widely used within adolescent samples and has consistently demonstrated strong psychometric properties.^38 39^ The Revised Child Anxiety and Depression Scale^40^ is a 47-item questionnaire with items corresponding to DSM-IV criteria for anxiety in the areas of social phobia, separation anxiety, obsessive compulsive disorder, panic disorder, generalised anxiety disorder and for major depressive disorder. Each item is rated on a 4-point Likert scale of frequency (never 0; sometimes 1; often 2; always 3), which are summed to produce subscale and total anxiety scores. The Strengths and Difficulties Questionnaire^41^ is a widely used behavioural screening questionnaire consisting of 25 items assessing emotional symptoms, conduct problems, hyperactivity and/or inattention, peer relationship problems and prosocial behaviour. Each item is rated as not true (0), somewhat true (1) or certainly true (2). A total difficulty score is calculated by summing scores from all subscales except the prosocial. In addition, an impact supplement assesses the degree of distress created by the child’s difficulties and the degree to which they interfere with home life, friendships, classroom learning and leisure activities. The five items are summed to produce a total ‘impact on everyday life’ score, which ranges from 0 to 10. The Sleep Condition Indictor (SCI)^42^ is an eight item self-report measure, assessing sleep and impact on daytime functioning over the past month on a 5-point scale. Item scores are summed to produce a total score ranging from 0 to 32. The SCI is an internally consistent (α = 0.86) measure with a clinical cut-off <17 correctly identifying 89% of those with probable DSM-5 insomnia disorder.^42^

#### Qualitative evaluation

We will use the semistructured interview developed in our initial study^43^ to assess participant’s experience of BlueIce, including use, ratings of satisfaction, helpfulness, ease of use and whether they would recommend it to a friend. In addition, we will assess the degree to which BlueIce was used and which parts of the app were used most often. This will only be completed by UC+BI at 12 weeks.

#### Economic analysis

A cost-effectiveness analysis will be undertaken alongside the RCT to estimate the incremental cost-effectiveness of UC +BI compared with UC, that is, incremental cost per unit of health outcome (primary outcome) and quality-adjusted life years (QALYs) using the NHS and social care perspective. In order to estimate QALYs, we will use the Child Health Utility 9D (CHU-9D). This preference-based generic HRQoL measure is designed specifically for use in the economic evaluation of healthcare interventions in young people.^44^ The CHU-9D contains nine dimensions (worried, sad, pain, tired, annoyed, schoolwork/homework, sleep, daily routine and activities), each with five levels of functioning rated for ‘today’. The CHU-9D has been validated for self-completion by young people (aged 7–17 years)^45^ and with CAMHS.^46^ Resource use and cost data will be collected from the participants recruited in the RCT using a resource use questionnaire. Data on self-reported resource use will be compared with the self-harm assessment data that are recorded in clinical case notes (CareNotes). Clinical records will be reviewed for accident and emergency attendances, out of hours contacts or primary and secondary care attendances following self-harm over two periods (6 months to baseline and baseline to 6 months). We will also quantify the number of face-to-face appointments and total number of hours of CAMHS input provided from baseline to 6 months. Incremental costs will be combined with data on effectiveness/health outcomes. National unit costs will be obtained from available sources including Personal Social Services Research Unit (PSSRU) (https://www.pssru.ac.uk/) and from the National NHS cost collection (https://www.england.nhs.uk/national-cost-collection/). Analyses will follow good practice for conducting economic evaluations in health technology assessment^47^ and findings will be reported using the CHEERS guidelines.^48^ Results will include disaggregated data, as well as synthesis of cost and outcome data, and will include presentation of cost-effectiveness plane,^49^ cost-effectiveness acceptability curves^50^ and detailed consideration of the broader impacts of the results reported. Robustness will be assessed through sensitivity analyses. Multiple imputations will be used to ‘fill-in’ missing cost and outcome data, making the assumption that the data are missing at random.^51^ If the young person is under 16, we will also ask their parent or guardian to complete both these questionnaires.
